#### Follow-Up at 24 Weeks

The final study visit will occur at 24 weeks, which will include clinician-rated and patient-rated study measures. After the last study visit at 24 weeks, participants will be offered the opportunity to try the treatment in the opposite study arm (the one they were not randomized to), or, if

initially randomized to escitalopram, to continue on the medication, if preferred. We believe that these extra, post-study treatment offerings will make participants more likely to enroll in the trial, since they will know that they will have the chance to try the treatment to which they were not randomized. Participants in the escitalopram arm who wish to try MBSR will be offered a spot in a class at no cost. Participants in the MBSR arm who wish to try escitalopram will be seen by a study MD/NP who will monitor medication effects for 2 months, after which time the patient will be referred back to his/her primary care provider or other clinician for continuation of care, if the patient desires to stay on the medication.

### Treatments

#### Mindfulness-Based Stress Reduction (MBSR)

MBSR is an 8-week group-based course developed by Jon Kabat-Zinn (1990) and colleagues at the University of Massachusetts' Center for Mindfulness. Weekly 2.5-hour long classes are given once a week, as well as one day-long weekend class during the 6th week. The classes instruct participants in the theory and practice of several forms of mindfulness meditation: a body scan (bringing awareness through the body systematically); breathing awareness (attention focused on the breath and other physical sensations); and mindfulness stretching exercises designed to bring awareness of the body and current experience of movement. Didactic teaching of the theory of mindfulness and experiential practice are both utilized during weekly classes and at-home CD-guided practice sessions.

If the MBSR course is canceled mid-way through, or is converted to an online platform for any reason (e.g., coronavirus), participants will be permitted to enroll in the online version of MBSR, or will be enrolled in a later course to finish their treatment.

#### Escitalopram (ESC)

During the 8 weeks of randomized treatment with ESC, subjects will be seen at baseline, post-baseline medication pick-up visit, weeks 1, 2, 4, 6, and 8 week endpoint, and at 12 week follow-up, (9 visits total) by a study physician/nurse practitioner. Georgetown University Medical Center's research pharmacy will be responsible for preparing the medication, which will be given to the participants by a study M.D. from baseline to week 12. Patients will take the pills each day at home. ESC will be initiated at 10 mg/day; which will be continued to week 2, when it will be increased to 20mg/day if well tolerated (or delayed if not). Medication adherence will be assessed by pill count and a standardized adherence measurement [68]. Side effects will be assessed at each visit and recorded. Participants will also be instructed to contact study staff immediately if any significant side effects, symptomatic worsening, or suicidal ideation develops in between visits. After week 12, if the patient desires to stay on the medication, s/he will be given a prescription by the study MD/NP., who will also start the process of transition to outpatient care so that the patient can continue treatment after the end of the study, if desired.

If in-person visits are not possible for any reason (e.g., coronavirus), the study medication will be shipped directly to the patient from the research pharmacy following the pharmacy protocols and the study visits will be conducted using telehealth videoconferencing or telephone contact.

#### Adherence Documentation

Subjects' attendance in MBSR classes will be recorded and subjects will record the number of minutes spent practicing with the free Google StopWatch application, or another time log application, or on paper, and will report the number of minutes to the research coordinator.

Medication adherence will be assessed by pill count and a standardized adherence measurement [64].

## Instruments and Scales

### Patient-Reported Outcomes

**Overall Anxiety Severity and Impairment Scale (OASIS)** is the primary patient-reported measure of anxiety symptoms. The OASIS is a 5-item, self-report measure used to assess overall anxiety levels across diagnostic groups. Items are rated on a likert scale from 0-4, with higher values indicating greater clinical anxiety symptom severity. The OASIS has demonstrated good validity and reliability transdiagnostically in psychiatric samples of individuals with anxiety disorders, including patients with primary GAD, SAD, or PD [30-32]. This measure has been utilized as the primary outcome measure for various randomized control trials investigating treatment effectiveness across GAD, SAD, and PD patient populations [33, 34].

To assess satisfaction/acceptability of treatment, we will use the **Client Satisfaction Questionnaire (CSQ)** [35] and the **Reactions to Treatment Questionnaire (RTQ)** [36]. To assess sleep outcomes, we will use the **Pittsburgh Sleep Quality Index (PSQI)**, a 24-item patient administered scale with demonstrated validity and reliability assessing subjective sleep quality [37], as well as the **PROMIS Sleep-Anxiety measure**, which consists of 13 items from the PROMIS Sleep Disturbance battery, that relate specifically to sleep disturbance resulting from worry, anxiety, or stress .

**The Beck Anxiety Inventory (BAI)** is a 21-item self-report inventory designed to measure severity of anxiety symptoms in psychiatric populations has high internal consistency, established validity, and test-retest reliability [38]. The BAI has both a cognitive and somatic subscale and has been used for over 20 years.

The **Difficulties in Emotion Regulation Scale- Short Form** (Kaufman et al. 2015) is an 18-item self-report measure that has established validity and is widely used for assessing emotion regulation style in adults.

The **Self-Compassion Scale (SCS)** [64] is a 26-item self-report instrument that uses a 5-point Likert scale for each item to assess compassion and kindness towards oneself, partially through seeing one's experiences as not unique and specific to the individual, but part of a larger human experience. The SCS has six subscales: Self-Kindness, Common Humanity, Mindfulness, Self-Judgment, Isolation, and Over-Identification. The SCS has demonstrated good reliability and validity in English and several other languages.

**The PROMIS - Emotional Distress** scales (ED) [39] will be used to assess emotional distress in the past 7 days, including depressive symptoms, anxiety symptoms, and anger. Another patient-reported outcome of anxiety, and worry in particular, is the Penn State Worry

Questionnaire (PSWQ) [40]. We will also use the Quick Inventory of Depressive Symptomatology, Self-Report, or QIDS-SR [41] to measure depression severity including suicidality.

To assess quality of life, we will use the **PROMIS - Satisfaction with Participation in Social Roles - Short Form (SPSR)** [42] that assess contentment with social roles, such as work and family responsibilities, within the past 7 days, and the **PROMIS - Ability to Participate in Social Roles and Activities - Short Form 4A (APSRA)** [42] that assess participants' perceived ability to perform their usual social roles and activities.

Adherence for the MBSR arm will be measured by class participation and a self-report Treatment Tracking log in REDCap, where participants will report the number of minutes that they spent meditating each day over the past week. Participants will be asked to track their meditation minutes using the free Google StopWatch application, or another time log application, or on paper.

The **Childhood Trauma Questionnaire (CTQ-28)** is a 28 item self-report questionnaire that assesses patients' history of childhood abuse and neglect and specifically focuses on emotional abuse, physical and emotional neglect, and sexual abuse. [61]

The **Life Events Checklist (LEC)** consists of a list of 17 items describing traumatic experiences (fire, exposure to toxic substances, etc), each which is checked off as "Happened to me", "Witnessed it", "Learned about it," "Part of my job," "Not sure," or "Doesn't apply." [62]

The **Health Performance Questionnaire (HPQ)** is a self-report survey measure of job performance [50]. The HPQ quantifies measures such as sickness absence and work performance. The HPQ is a valid and reliable tool for estimating the indirect workplace costs of illness [51]. It is also sensitive to changes [51] and when used longitudinally, the HPQ can reveal the cost-effectiveness of treatment.

The **Quick Inventory of Depressive Symptomatology, Self-Report (QIDS-SR)** is a 16-item self-report questionnaire that assesses depressive symptoms, including suicidality [41]. This tool is widely used and has established validity.

The **Adherence Questionnaire (AQ)** is a 2-item questionnaire that is used to determine what proportion of the time between visits the participant took their study medication as recommended, and to establish the reason(s) for deviating from the recommended dose (e.g., forgot, side effects, thought not needed, etc.).

### Clinician-Rated Outcomes

The primary measure of anxiety symptoms is the **Clinician Global Impression-Severity Scale (CGI-S)**. Additionally, we will utilize the **Clinical Global Impression-Improvement (CGI-I)** Scale [45-48]. The CGI has excellent psychometric properties, is treatment sensitive, and highly correlated with anxiety and depression scales across disorders [49].

The **MINI International Neuropsychiatric Interview** **MINI** will be administered by a trained interviewer, and will take approximately 25 minutes. This short, diagnostic structured interview

has proven to provide reliable diagnoses (Lecrubier et al., 1997) and is considerably shorter than other structured diagnostic interview tools.

The **Structured Interview Guide for the Hamilton Anxiety Scale (SIGH-A)** is designed to assist clinicians in evaluating anxiety symptoms through the HAM-A. The 14-item HAM-A (Hamilton 1959) was developed to assess general anxiety symptoms in a clinical population and has proven sensitive to change with treatment. The SIGH-A provides specific and detailed rating guidelines for the purposes of administering and scoring the HAM-A, and has demonstrated high interrater and test-retest reliability [59].

The **Panic Disorder Severity Scale (PDSS)** is a semi-structured interview of panic symptom severity. It contains 7 items assessing multiple dimensions of PD severity, including a) frequency of panic attacks, b) distress during panic attacks, c) anticipatory anxiety, d) agoraphobic fear and avoidance, e) interoceptive fear and avoidance, f) impairment of work and social functioning. The PDSS is a widely applied measure of the severity of panic disorder symptoms [58].

The **Liebowitz Social Anxiety Scale (LSAS)** is a reliable and validated measure of social anxiety, that assesses both fear and anxiety about common social situations, as well as avoidance components of social anxiety [60].

The **Frequency, Intensity, and Burden of Side Effects Ratings (FIBSER)** is a 3-item, validated measure to assess the frequency, intensity, and interference of side effects due to study treatment. The **Adverse Events Form** is a form for the study clinician to fill out while interviewing patient which lists all adverse events and side effects due to study treatment.

The **Concomitant Treatment Form** is a form for the study clinician to fill out while interviewing patient which indicates forms of treatment that the patient may have started or stopped.

The **Clinician Suicide Assessment Form** is a form for the study clinician to fill out to assess the severity of a patient's suicidal ideation.

## VIII. BIOSTATISTICAL ANALYSIS

### Basic Statistical Analyses:

Initial statistical analysis will provide descriptive statistics on the demographic and clinical characteristics of the study participants using means, standard deviations, median and range for continuous variables and frequencies and percentages for categorical variables. To examine potential differences between the groups at baseline, descriptive statistics will be obtained for each group and compared statistically using two-sample t-tests, nonparametric rank tests, chi-square and Fisher's exact test as appropriate. All outcome variables will be summarized using similar methods for pre and post-treatment and 12 week follow-up.

### Outcome Assessment:

The treatment response (CGI-I) will be compared by groups and tested via confidence intervals to examine the precision of non-inferiority. A review of methods for non-inferiority studies on behavioral treatments (Steinert et al 2017) found that of the eight published studies reviewed, the effect size used in the non-inferiority margin calculation ranged between  $d=0.26$  and  $d=0.6$ . One of the examples in this review was a study of CBT that included all anxiety disorders,

similar to the sample in our current proposal (Norton and Barrera 2012). For this study, the researchers also surveyed the literature to determine the best way to calculate a non-inferiority margin with a transdiagnostic sample. They proposed that the non-inferiority margin be computed by multiplying the standard deviation of the particular outcome measure by the meta-analytically derived effect size, deriving their approach from a standard methodology recommended for rigorous equivalence designs (e.g. see Jones et al 1996). Using this calculation method, and using the SD of 1.1 points for CGI change scores from other escitalopram trials across anxiety disorders (see summary in Bandelow et al 2006), would have yielded a non-inferiority margin of 0.66 unit on the CGI-S (by multiplying 1.1 by 0.6). However, to be more conservative, a non-inferiority margin of 0.33 ( $0.3 \times 1.1$ ) was used in our sample size calculations. This margin represents a difference of 1/3 of a point on the CGI-S score. We also defined a largest-clinically-acceptable non-inferiority margin following the literature by determining the halfway point between these two numbers (0.66 and 0.33) to get 0.495, ( $0.45 \times 1.1$ ) such that a difference of 0.495 or smaller will still allow us to declare MBSR to be noninferior to escitalopram treatment. Further support for the appropriateness of this margin comes from the literature where a change of 1.0 unit, substantially higher than a margin of 0.495, is considered the Minimal Clinically Important Change (MCID) score for the CGI-S and has been used to anchor definitions of clinically significant change across other measures.

Therefore, the null hypothesis for the non-inferiority test will be that the drug group's mean CGI-S score reduction at endpoint is greater than that of the MBSR group by at least 0.495 points (for this scale, higher scores indicate higher severity and greater reduction indicated greater improvement). In other words, if the MBSR group's post-intervention mean CGI-S score change is less than that of the drug group by not more than 0.495 points we will consider MBSR to be non-inferior to the standard pharmacotherapy escitalopram. Based on these parameters, the required analysis sample size with equal allocation to achieve an 80% power at significance level of 0.05 will thus be N=276 study completers.

To conservatively address attrition, we estimate our projected dropout rate to be 25% and therefore plan to randomize 368 participants with a 1:1 ratio to each group, yielding 276 completers after drop-out. Of note, many published non-inferiority trials have relied on intent-to-treat analyses that are more liberal than our proposed completer analysis. We also propose to conduct sensitivity analyses with the intent-to-treat sample as a follow-up to our primary completer analysis.

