#### **IV. SPECIFIC AIMS (Research Objectives)**

We will assess the comparative effectiveness of Mindfulness-Based Stress Reduction (MBSR) compared to escitalopram (ESC) for patients with anxiety disorders (generalized anxiety disorder, panic disorder, agoraphobia, and social anxiety disorder), by randomizing patients to eight weeks of (1) MBSR or (2), flexible-dose escitalopram. This two-arm, three-site, randomized, controlled study will use a standard non-inferiority study design which incorporates previous data demonstrating that escitalopram is an effective treatment for anxiety and has been proven against pill placebo. Based on non-inferiority driven power calculations (see Analysis plan), we plan to randomize 368 patients to either MBSR or medication. We expect that 276 will complete the protocol after 25% dropout; however treatment satisfaction including dropout and intent-to-treatment outcomes will also be important assessments to guide conclusions about patient preferences and treatment responses. This non-inferiority randomized design with standardized blinded assessments provides the most rigorous comparison data regarding comparison of the novel treatment of MBSR to a gold standard treatment, escitalopram. This study will provide crucial information to patients about effective and acceptable treatment strategies for anxiety.

We will examine several secondary outcome measures and exploratory outcomes. Overall Anxiety Severity and Impairment Scale (OASIS) is the secondary measure of anxiety symptoms. To assess satisfaction/acceptability of treatment, we will use the Client Satisfaction Questionnaire (CSQ) and the Reactions to Treatment Questionnaire (RTQ). To assess sleep outcomes, we will use the Pittsburgh Sleep Quality Index (PSQI), The Beck Anxiety Inventory (BAI) is a 21-item self-report inventory designed to measure severity of anxiety symptoms in

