\*\*these procedures will only be completed if pre-existing records are not obtainable

Participants will be paid a total of \$160 participation in the study. If a patient misses a treatment visit, the provider (MBSR instructor or Medical Rater) will reach out to them and work with the patient to minimize any barriers. For all assessment visits, including the follow-up visits at 12 and 24 weeks, we will offer flexible visits which can be done over the phone, videoconferencing, and/or electronically, if needed. In order to reduce missing data, as well as reducing the likelihood that treatment related dropout biases the available data for this effectiveness study in which treatment satisfaction, tolerability, adherence and response are all clinically relevant, to the extent feasible, we will follow subjects who miss treatment visits or drop out of the assigned protocol (either voluntarily, or removed by the study due to adverse effects) and continue to collect their assessment data and include them in the analysis according to their original assignment.

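### The sole primary non-inferiority test uses an undefined completer set, at odds with the commitment to analyse treatment dropouts as assigned, and its bias can go either way

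*Protocol*

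**What the plan says.** Three places in the protocol bear on who is in the deciding analysis.

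- **Section VIII, Outcome Assessment.** The primary test is on completers and the as-randomised set comes second: "We also propose to conduct sensitivity analyses with the intent-to-treat sample as a follow-up to our primary completer analysis". The reason offered is that "many published non-inferiority trials have relied on intent-to-treat analyses that are more liberal than our proposed completer analysis". The trial is sized on 276 completers out of 368 randomised, with 25% dropout.
- **Section VII, text below the Table of Assessments.** Follow-up, to the extent feasible, covers people who miss treatment visits or "drop out of the assigned protocol (either voluntarily, or removed by the study due to adverse effects"). The team will "continue to collect their assessment data and include them in the analysis according to their original assignment". One stated purpose is "reducing the likelihood that treatment related dropout biases the available data for this effectiveness study".
- **Section IV.** Here "treatment satisfaction including dropout and intent-to-treatment outcomes will also be important assessments to guide conclusions", but intent-to-treat is given no rank and no part in the decision.

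No section says what makes a participant a completer. Section IV describes the 276 as those expected to finish the protocol, which leans toward treatment completion. Section VIII speaks of study completers, which could also mean anyone still assessed at the endpoint.

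**The concern.** Section VII names a source of bias and plans data collection to guard against it. Section VIII then rests the non-inferiority claim on a set that may leave those data out. As written, non-inferiority can be declared on a subset formed after randomisation, and nothing says what follows if the intent-to-treat result disagrees.

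The stated justification does not repair this. Intent-to-treat can dilute a real difference in a non-inferiority trial, which is a good reason to run both analyses. It does not make the completer set conservative. Removing people after randomisation shifts the contrast whenever the share removed, or how they fare relative to those who stay, differs between arms. Section IX gives grounds to expect different reasons for leaving: distress, scheduling burden or lack of benefit with MBSR, and drug side effects with escitalopram.

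**Working it through.** **The plan's own figure.** Inputs from Outcome Assessment: SD of CGI change 1.1, power 80%, significance level 0.05 (sidedness not stated). The 0.33 margin is the one that "was used in our sample size calculations". With a true difference of 0 and one-sided 0.05:

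n per arm = 2 × 1.1² × (1.645 + 0.842)² / 0.33² = 137.4, rounded up to 138, so N = 276. Then 276 / 0.75 = 368.

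Both figures reproduce. One-sided 0.025 would give 350, so one-sided 0.05 is my inference from the match. The decision uses the wider margin, "such that a difference of 0.495 or smaller will still allow us to declare MBSR to be noninferior to escitalopram treatment".

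**Bias of the completer contrast.** Let d be the dropout share in an arm, and g the mean CGI-S improvement of completers minus that of dropouts. Then

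bias = d(MBSR) × g(MBSR) − d(ESC) × g(ESC), positive values favouring MBSR.

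**False non-inferiority** when MBSR is truly worse by exactly the margin = Φ(bias / SE − 1.645), with SE = 1.1 × √(2/138) = 0.132.

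The protocol gives neither d by arm nor g. Every row below is therefore an assumption. All keep 25% dropout overall. The 1.0-point gap is scaled to the protocol's own minimal important change on the CGI-S.

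| Dropout MBSR / ESC | Gap MBSR / ESC | Bias | Share of 0.495 | False non-inferiority |
|---|---|---|---|---|
| 25% / 25% | equal | 0 | 0% | 5% |
| 30% / 20% | 1.0 / 1.0 | 0.30 − 0.20 = +0.10 | 20% | Φ(−0.89) ≈ 19% |
| 20% / 30% | 1.0 / 1.0 | 0.20 − 0.30 = −0.10 | −20% | Φ(−2.40) ≈ 0.8% |
| 25% / 25% | 1.0 / 0.5 | 0.25 − 0.125 = +0.125 | 25% | Φ(−0.70) ≈ 24% |
| 35% / 15% | 1.0 / 1.0 | 0.35 − 0.15 = +0.20 | 40% | Φ(−0.13) ≈ 45% |

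If the test is one-sided 0.025, the errors for +0.10, −0.10, +0.125 and +0.20 are about 11%, 0.3%, 16% and 33%, against 2.5%.

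**Power if both analyses must succeed** (true difference 0, margin 0.495, one-sided 0.05):

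- Completers, 138 per arm: Φ(0.495/0.132 − 1.645) = 98.2%.
- As randomised: 99.6% if all 184 per arm are rated, 98.2% if only 138 are.
- Joint power is at least the sum of the two minus 1: 0.982 + 0.982 − 1 = 96.4% in the worse case.

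**The case against.** The strongest defence is that the two sections can be read together. Section VII does not say that dropouts enter the primary analysis. Section VIII does plan an intent-to-treat analysis, and under Multivariate Analyses it adds mixed models of the primary outcome that use the repeated measures and carry a non-inferiority assessment. On this reading dropouts' data are collected and analysed as assigned, only not in the first-ranked test. A completer analysis beside intent-to-treat is also accepted practice in a non-inferiority trial, and a definition of completer may sit in an analysis plan that is not at hand.

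Much of this stands. The conflict is one of ranking, and a reader who infers that dropouts' outcomes are certainly excluded from the primary test goes further than the text, because that depends on the undefined term. What the defence does not supply is a role for any as-randomised analysis in the decision. The mixed models are labelled secondary, and the coefficient they test is an average over all time points, not the endpoint contrast.

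A reader might also infer that the completer analysis is expected to favour MBSR by half the margin. That needs 25% dropout in each arm, MBSR dropouts a full point worse than completers and escitalopram dropouts no worse at all: 0.25 × 1.0 − 0.25 × 0 = 0.25, with an error near 60%. Nothing in the protocol supports that combination over the others, and equal dropout with equal gaps gives no bias.

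**Conclusion.** The point holds in a limited form and should be fixed. The protocol makes an undefined completer set the only primary test, justifies this with a general claim that does not hold, and leaves it unreconciled with its commitment to analyse dropouts as assigned.

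The bias may be zero or go either way. In the illustrations it runs from −0.10 to +0.20 CGI-S points, and reversing the 35%/15% row would give −0.20. On the side favouring MBSR this is 20% to 40% of the 0.495 margin, with false non-inferiority of about 19% to 45% instead of 5%. These figures rest on assumed dropout shares and gaps, on the protocol's SD of 1.1 with 138 per arm, and on one-sided 0.05. They show what completer selection can do, not what it will do here. If completer means anyone with an endpoint CGI-S, treatment dropouts who are assessed already count and the concern shrinks to those not assessed.

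**What to change.** 1. Define completer, and reconcile section VII with Outcome Assessment in section VIII.
2. Analyse all randomised participants in their assigned arm, using every endpoint CGI-S collected whether or not treatment was finished. A likelihood-based mixed model with a week-8 contrast is one suitable choice. Since it does not protect against data missing not at random, add a sensitivity analysis for that case.
3. Declare non-inferiority only if both this analysis and the completer analysis meet the margin.
4. Replace the sentence on intent-to-treat being more liberal with a statement that either analysis can be biased in either direction.

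The cost is mainly wording, because the follow-up data are already to be collected. Requiring both analyses needs no alpha adjustment and no more patients, and loses little power at the 0.495 margin. If the decision margin were instead 0.33, the completer test alone has 80% power, so the joint requirement would fall below that.
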